**10. Distribution of patients at various sites and duration of study:**

10.1 Distribution of patients:

| **Hospital number** | **Hospital** | **Person in charge** | **Number of cases** |
| --- | --- | --- | --- |
| 01 | Peking Union Medical College Hospital | [name] | **Competitive enrollment** |
| 02 | Peking University First Hospital | [name] |
| 03 | Bethune International Peace Hospital | [name] |
| 04 | Nanjing Drum Tower Hospital | [name] |
| 05 | The Second Affiliated Hospital of Sun Yat-sen University | [name] |
| 06 | West China Hospital of Sichuan University | [name] |
| 07 | China-Japan Union Hospital of Jilin University | [name] |
|  | **Total** |  | **90** |

10.2 Study progress:

Initiation of study: April 2010

Subject inclusion: April 2010

End of subject inclusion: October 2010

End of observation: October 2011

Statistical analysis: November 2011

Summary report: December 2011

Attachment I: Trial Flow Chart

Attachment II: Health Assessment Questionnaire (HAQ)

Attachment III: Sharp Score Criteria

Attachment IV: Wrist X-ray Staging Criteria for Rheumatoid Arthritis (ACR)

Attachment V: Table of Swollen and Tender Joint Count

**Attachment I:**

**Trial Flow Chart**

| **Work Contents** | **Baseline Period** | **Treatment Period** | | | |
| --- | --- | --- | --- | --- | --- |
| **D-7~0** | **12W±7d** | **24W±7d** | **36W±7d** | **52W±7d** |
| **Informed consent** | **√** |  |  |  |  |
| **Inclusion criteria** | **√** |  |  |  |  |
| **Exclusion criteria** | **√** |  |  |  |  |
| **Medical history collection** | **√** |  |  |  |  |
| **Vital signs** | **√** | **√** | **√** | **√** | **√** |
| **Physical examination** | **√** | **√** | **√** | **√** | **√** |
| **HBs-Ag/HCV-Ab** | **√** |  |  |  |  |
| **Tuberculin test (PPD)** | **√** |  |  |  |  |
| **Chest X ray** | **√** |  |  |  | **√** |
| **Disease status assessment** | **√** | **√** | **√** | **√** | **√** |
| **Routine blood test** | **√** | **√** | **√** | **√** | **√** |
| **Urinalysis** | **√** | **√** | **√** | **√** | **√** |
| **Blood chemistry test** | **√** | **√** | **√** | **√** | **√** |
| **Erythrocyte sedimentation rate (ESR)** | **√** | **√** | **√** | **√** | **√** |
| **C-reactive protein (CRP)** | **√** | **√** | **√** | **√** | **√** |
| **Rheumatoid factor** | **√** |  | **√** |  | **√** |
| **Anti-CCP (2nd Generation) antibody** | **√** |  |  |  |  |
| **Antinuclear antibody (ANA)** | **√** |  | **√** |  | **√** |
| **ECG** | **√** | **√** | **√** | **√** | **√** |
| **X-ray of both hands (including wrist joint)** | **√** |  | **√** |  | **√** |
| **MRI** | **√** |  |  |  | **√** |
| **Medication administration record** |  | **√** | **√** | **√** | **√** |
| **Documentation of concomitant medications** | **√** | **√** | **√** | **√** | **√** |
| **Adverse event evaluation** |  | **√** | **√** | **√** | **√** |
| **Clinical efficacy evaluation** |  | **√** | **√** | **√** | **√** |

**Attachment II:**

**Health Assessment Questionnaire (HAQ)**

Each subject assesses his/her own ability of daily living, including 20 indicators such as dressing, standing, eating and drinking, walking, hygiene, grasping. The assessment is divided into four levels:

0= not difficult; 1= slightly difficult; 2=very difficult; 3= incapable.

| **When doing the following activities in the past week:** | | **Score** |
| --- | --- | --- |
| 01 | Put on clothes (Fasten shoelaces and buttons)? |  |
| 02 | Comb your hair? |  |
| 03 | Stand up from a chair without support from hands? |  |
| 04 | Get into bed, get out of bed? |  |
| 05 | Raise a glass to drink water? |  |
| 06 | Cut vegetables? |  |
| 07 | Unscrew a bottle cap? |  |
| 08 | Walk on the flat ground outdoors? |  |
| 09 | Ascend the stairs for 5 steps? |  |
| 10 | Dry yourself after bathing? |  |
| 11 | Get up from the toilet seat or sit down by yourself? |  |
| 12 | Bend down to pick up things on the floor? |  |
| 13 | Reach out for the clothing on the coat rack? |  |
| 14 | Turn on and off a water faucet? |  |
| 15 | Get on and off (buses, cars)? |  |
| 16 | Shop around? |  |
| 17 | Do household chores like cleaning the floor? |  |
| 18 | Walk for 1 kilometer? |  |
| 19 | Participate in an activity you enjoy? |  |
| 20 | Sleep well at night? |  |
| **Total score** | |  |
| **Average score** | |  |

**Attachment III:**

**Sharp Score Criteria**

**Joint Erosion Score (ES)**

The simple scoring method is: The joint is divided into 4 equal parts, and 1 point is given if there is erosion in each part. If there is an intersection part, it is scored according to one fifth of the eroded area of the joint, with one point for every one fifth.

[figure not shown]

With the erosion scores being 0-5, the judgment criteria are as follows:

0 = no erosion;

1 = 1 quarter joint part is eroded alone, or the eroded area of the joint is ≤ 20%;

2 = 2 quarter joint parts are eroded respectively, or 20% < joint eroded area ≤ 40%;

3＝3 quarter joint parts are eroded respectively, or 40% < joint eroded area ≤ 60%；

4＝4 quarter joint parts are eroded respectively, or 60% < joint eroded area ≤ 80%；

5 = the joint is completely destroyed.

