**7. Efficacy evaluation:**

7.1 Primary endpoints:

Improvement in Sharp score of X-ray of affected joints.

7.2 Secondary endpoints:

1. Proportion of subjects reaching ACR20, ACR50 and ACR70: ACR50 and ACR70 are defined as 50% and 70% improvement respectively using the same criteria as ACR20.
2. Average changes of ACR core parameters relative to the baseline level
3. Average change of HAQ score from baseline to Week 52
4. Time for each treatment group to reach ACR20, 50 and 70
5. The proportion of subjects with low disease activity at each visit
6. The proportion of subjects achieving disease remission at each visit
7. MRI changes (joint space narrowing and bone erosion)

7.2.1 The response definition of ACR20 is: there is 20% improvement in the number of swollen and tender joints (28), as well as 20 % improvement in at least 3 of the 5 following items:

1. The VAS score of pain assessed by the subject;
2. The VAS score of overall disease condition assessed by the subject;
3. The VAS score of overall disease condition assessed by investigator;
4. Health Assessment Questionnaire (HAQ);
5. Acute phase reactant (ESR or CRP).

7.2.2 DAS28:

[figure not shown]
(28 joints)

The disease activity score of 28 joints will be calculated as follows:

DAS28 = 0.56 × + 0.28 × + 0.7 × ln(ESR) + 0.014 × GH

TJC: Tender joint count, SJC: Swollen joint count, ESR: erythrocyte sedimentation rate (in mm/h), GH: general health status expressed in the 100 mm VAS.

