**9. Statistical methods:**

9.1 Selection of statistical analysis data:

Intent-to-treat (ITT): all subjects eligible and enrolled after screening and having taken at least one dose of the drug and received at least one post-treatment effectiveness evaluation; LOCF (last observation carry-forward) will be adopted for those subject’s data not observed during the whole treatment course, that is, estimating the missing values of important indicators using the closest observed data. The ITT analysis will be used in this trial.

Safety population: it includes all subjects having taken at least one dose of the drug and received at least one post-treatment safety evaluation.

9.2 Statistics Analysis Plan:

Statistical analysis will be carried out using the SAS statistical analysis software. A sample size of 90 patients was estimated for the open label period with the assumption that mean mTSS CRF was -0.5±1.0 in the MTX plus rhTNFR:Fc group, and 2.5±5.0 in the MTX group at week 52. A sample size of 25 patients per treatment group was calculated to be necessary for more than 80% power to reject the null hypothesis of no difference among the treatment groups with an α of 0•05. Assuming loss of patients, the study required a minimum of 30 patients in each group. Two-sided test will be used for all statistical tests, and the difference tested will be considered as statistically significant if the P value is equal to or less than 0.05. Measurement data will be statistically described using mean±SD (standard deviation). Paired t-test will be used for intra-group differences before and after the treatment. Enumeration data will be statistically described using frequency (constituent ratio).

Dropout analysis: Calculate the dropout rates and the rates of dropout due to AE.

Efficacy analysis: The paired t test or nonparametric test or chi-square test will be used to evaluate the efficacy indexes.

Safety analysis: Calculate the incidence rate of adverse events and tabulate the AEs occurring during the trial, normal/abnormal changes in laboratory findings before and after the trial, as well as relationships of abnormal changes with the investigational drug

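### Attachment III grades erosions on two non-equivalent scales with no order of precedence, so a worsening joint with two or more eroded quarters can lose up to 1 to 3 points on the primary Sharp score

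*Protocol*

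**What the plan says.** Protocol section 7.1 names a single primary endpoint, "Improvement in Sharp score of X-ray of affected joints". Attachment III defines the erosion part of that score, from 0 to 5 per joint, by two rules.

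- Quarter count: "The joint is divided into 4 equal parts, and 1 point is given if there is erosion in each part".
- Eroded area: "If there is an intersection part, it is scored according to one fifth of the eroded area of the joint", at one point per fifth.

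The grade list then pairs the two. Grade 1 is "1 quarter joint part is eroded alone, or the eroded area of the joint is ≤ 20" (per cent). Grade 4 is "4 quarter joint parts are eroded respectively, or 60% < joint eroded area ≤ 80" (per cent). Grades 2 and 3 follow the same pattern, with area bands up to 40% and 60%. Grade 5 is "5 = the joint is completely destroyed".

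Attachment III does not say which rule prevails when a joint meets two grades. Nor does it say that a joint keeps the same rule across its films, which the flow chart in Attachment I schedules at baseline, Week 24 and Week 52.

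**The concern.** A progression score should not fall when damage grows. The quarter count ignores lesion size, while the area rule ignores how many quarters are affected. Writing *or* between them treats them as interchangeable, yet for small scattered erosions they differ by several grades. If one lesion crossing a quarter line moves the joint from the first rule to the second, the recorded score can drop although more bone is eroded. The endpoint would count that drop as improvement.

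Even without a switch between films, two readers could give the same film grade 4 or grade 1 and both be within the text. Either way, measurement error enters the only primary endpoint.

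**Working it through.** **Inputs.** The two rules and the grade list are from Attachment III, and the endpoint from section 7.1. The planning assumption is from section 9.2: "mean mTSS CRF was -0.5±1.0 in the MTX plus rhTNFR:Fc group, and 2.5±5.0 in the MTX group at week 52", with 25 per group for more than 80% power, two-sided 0.05.

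**1. The plan's own figure.** The protocol gives no figure for the erosion rule; its only related figure is the sample size. The difference is 2.5 − (−0.5) = 3.0. With 25 per group, the standard error is √(1.0²/25 + 5.0²/25) = √1.04 = 1.02. Welch t-test power is 80.8% at 25 per group and 79.1% at 24. The stated 25 is reproduced and is not in dispute.

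**2. Overlap on one film.** Let k be the number of separately eroded quarters and A the eroded area in per cent. The count grade is k; the area grade is A/20 rounded up. With four small separate erosions and A = 15, the count grade is 4 and the area grade is 15/20 = 0.75, rounded up to 1. One joint meets two grades three points apart.

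**3. Change between films, literal reading.** The joint scores k before the crossing and A/20 rounded up afterwards, where A is the new area. The smallest possible area grade is 1, so the largest loss is k − 1. A loss occurs when A ≤ 20(k − 1).

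| Quarters eroded before (k) | Change at crossing | Score falls if new area is at most |
|---|---|---|
| 1 | 0 to +2 | never |
| 2 | −1 to +2 | 20% |
| 3 | −2 to +2 | 40% |
| 4 | −3 to +1 | 60% |

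The upper ends assume that the crossing lesion reaches at most one further quarter and that an area above 80% scores 5. The losses do not depend on either assumption.

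Example: four separate erosions with 12% total area score 4. One grows across a line and the total becomes 16%, which scores 1. Damage rose and the recorded change is −3.

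**4. Other readings of the same text.**

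| Reading | Largest loss |
|---|---|
| Whole joint switches to area | 3 |
| Only the crossing lesion is scored by area | 0 if it merges with no other; 1 if two lesions merge; 3 only if all four merge within 20% of the area |
| *Or* means the higher grade | 0 |

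**5. Direction.** Compare the area grade with the quarter count when m quarters are involved. For illustration only, take A as uniform between 0 and 25m per cent. The area grade is lower with probability 20(m − 1)/(25m), equal with 20/(25m), and higher with 5m/(25m).

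- m = 2: 40% lower, 40% equal, 20% higher; mean difference −0.2.
- m = 3: 53%, 27%, 20%; mean −0.6.
- m = 4: 60%, 20%, 20%; mean −1.0.

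The area rule therefore tends to score below the count when erosions are small, but can score a point above it when they are extensive.

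**6. After the fix.** If the higher grade is recorded, the example in step 3 scores 4 on both films, and the largest artefactual loss is 0.

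**The case against.** The strongest reply is that the whole-joint switch is only one reading. In the intersection sentence, *it* can mean the crossing lesion alone, and *or* can mean that the higher grade counts. Step 4 shows that these readings reduce or remove the loss. A figure at this point in Attachment III is not shown and may illustrate the intersection case, and separate reading instructions may exist. This stands as a limit on the claim: the fall is a consequence of the literal wording, not of every possible wording. It does not remove the problem. The text states neither alternative, and a rule under which one film may score 4 or 1 is itself a defect.

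Three stronger conclusions are tempting, and the documents support none of them.

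- **That progression is understated as a matter of fact.** The direction depends on lesion size (step 5). Artefactual falls on MTX would shrink the planned difference, but falls on combination therapy would widen it.
- **That the entry criteria put every patient at risk.** Section 4.1 requires at least one erosion, and a joint with one eroded quarter never loses points. A fall needs at least two separately eroded quarters in the same joint. A fall of 3 needs all four, with a later area of at most 20%.
- **That the trial loses a stated amount of power.** The Welch arithmetic is simple: at 25 per group, differences of 2.8, 2.6 and 2.4 give 75.3%, 68.9% and 62.0%. But reductions of 0.2 to 0.6 points have no source in the protocol. Setting a 3-point fall in one joint against a 3.0-point difference in group means is not like for like either.

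**Conclusion.** The concern holds as a defect in the scoring rule. Attachment III contains two non-equivalent erosion scales without precedence, so one joint can meet grades as far apart as 4 and 1. On the literal reading, a worsening joint with 2, 3 or 4 separately eroded quarters can lose up to 1, 2 or 3 points. This can understate progression on the primary endpoint when erosions are small, and it adds noise.

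The size per joint rests on the whole-joint reading and on eroded area not decreasing. The size for the trial cannot be given, because the protocol reports no frequency of multi-quarter joints, no lesion sizes and no growth rates. The sample size of 25 per group is unaffected as a calculation. Because the protocol itself states this rule for its only primary endpoint, Attachment III is the place to correct it.

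**What to change.** Add one rule to Attachment III: on every film, each joint is graded both by the number of quarters containing erosion and by eroded-area class, and the higher of the two grades is recorded, in the same way at baseline, Week 24 and Week 52. For the guarantee to hold, a quarter should count whenever any erosion lies in it, including part of a lesion that crosses a line; otherwise merging lesions could still lower the count. Neither grade can then fall while erosion grows, so the higher one cannot either.

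Fixing one method per joint after seeing all its films would also prevent false falls. However, it would choose the method from later films and re-score earlier visits, including the Week 24 comparison. It would also show no change for growth within one area class, such as 15% to 19%.

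The cost is small: readers record two classes for each eroded joint, with no extra films, readers or patients. A small lesion straddling a line will score one point per quarter touched, which the instructions should state openly.

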**Joint Space Narrowing Score, JSN:**

The JSN scores are 0-4.

0= normal

1 = punctiform protrusion, asymmetric, with the narrowing degree < 25%;

2 = Narrowing degree of 25-60%;

3＝Narrowing degree of 60-99％；

4 = complete rigidity or dislocation.

**Attachment IV:**

**Wrist X-ray Staging Criteria for Rheumatoid Arthritis (ACR)**

| Level I: Osteoporosis of joints or under articular surfaces. |
| --- |
| Level II: Subarticular osteoporosis, with occasional cystic destruction of articular surface or bone erosion and destruction. |
| Level III: Obvious articular surface damage or bone erosion damage, joint space narrowing, joint subluxation and other changes. |
| Level IV: Other lesions than Phase II and III lesions, with fibrous or bony rigidity. |

**Attachment V: Joint swelling and tenderness**

The swollen and tender joint count will be recorded (SJC, 66 joints counted; TJC, 8 joints counted):

Table of Swollen and Tender Joint Count

| Right side | | | Joint | Left side | | |
| --- | --- | --- | --- | --- | --- | --- |
| Tender  1 2 3 | Swelling  1 2 3 | NE |  | NE | Tender  1 2 3 | Swelling  1 2 3 |
| □ □ □ | □ □ □ | □ | Temporal-mandibular joint | □ | □ □ □ | □ □ □ |
| □ □ □ | □ □ □ | □ | Sternoclavicular joint | □ | □ □ □ | □ □ □ |
| □ □ □ | □ □ □ | □ | Acromioclavicular joint | □ | □ □ □ | □ □ □ |
| □ □ □ | □ □ □ | □ | ***Shoulder joint*** | □ | □ □ □ | □ □ □ |
| □ □ □ | □ □ □ | □ | ***Elbow joint*** | □ | □ □ □ | □ □ □ |
| □ □ □ | □ □ □ | □ | ***Wrist joint*** | □ | □ □ □ | □ □ □ |
| □ □ □ | □ □ □ | □ | ***First metacarpophalangeal joint*** | □ | □ □ □ | □ □ □ |
| □ □ □ | □ □ □ | □ | ***Second metacarpophalangeal joint*** | □ | □ □ □ | □ □ □ |
| □ □ □ | □ □ □ | □ | ***Third metacarpophalangeal joint*** | □ | □ □ □ | □ □ □ |
| □ □ □ | □ □ □ | □ | ***Fourth metacarpophalangeal joint*** | □ | □ □ □ | □ □ □ |
| □ □ □ | □ □ □ | □ | ***Fifth metacarpophalangeal joint*** | □ | □ □ □ | □ □ □ |
| □ □ □ | □ □ □ | □ | ***Thumb interphalangeal joint*** | □ | □ □ □ | □ □ □ |
| □ □ □ | □ □ □ | □ | ***Second proximal interphalangeal joint*** | □ | □ □ □ | □ □ □ |
| □ □ □ | □ □ □ | □ | ***Third proximal interphalangeal joint*** | □ | □ □ □ | □ □ □ |
| □ □ □ | □ □ □ | □ | ***Fourth proximal interphalangeal joint*** | □ | □ □ □ | □ □ □ |
| □ □ □ | □ □ □ | □ | ***Fifth proximal interphalangeal joint*** | □ | □ □ □ | □ □ □ |
| □ □ □ | □ □ □ | □ | Second distal interphalangeal joint | □ | □ □ □ | □ □ □ |
| □ □ □ | □ □ □ | □ | Third distal interphalangeal joint | □ | □ □ □ | □ □ □ |
| □ □ □ | □ □ □ | □ | Fourth distal interphalangeal joint | □ | □ □ □ | □ □ □ |
| □ □ □ | □ □ □ | □ | Fifth distal interphalangeal joint | □ | □ □ □ | □ □ □ |
| □ □ □ | □ □ □ | □ | Hip joint | □ | □ □ □ | □ □ □ |
| □ □ □ | □ □ □ | □ | ***Knee joint*** | □ | □ □ □ | □ □ □ |
| □ □ □ | □ □ □ | □ | Ankle joint | □ | □ □ □ | □ □ □ |
| □ □ □ | □ □ □ | □ | Tarsal joint | □ | □ □ □ | □ □ □ |
| □ □ □ | □ □ □ | □ | First metatarsophalangeal joint | □ | □ □ □ | □ □ □ |
| □ □ □ | □ □ □ | □ | Second metatarsophalangeal joint | □ | □ □ □ | □ □ □ |
| □ □ □ | □ □ □ | □ | Third Metatarsophalangeal joint | □ | □ □ □ | □ □ □ |
| □ □ □ | □ □ □ | □ | Fourth metatarsophalangeal joint | □ | □ □ □ | □ □ □ |
| □ □ □ | □ □ □ | □ | Fifth metatarsophalangeal joint | □ | □ □ □ | □ □ □ |
| □ □ □ | □ □ □ | □ | First interphalangeal joint | □ | □ □ □ | □ □ □ |
| □ □ □ | □ □ □ | □ | Second interphalangeal joint | □ | □ □ □ | □ □ □ |
| □ □ □ | □ □ □ | □ | Third interphalangeal joint | □ | □ □ □ | □ □ □ |
| □ □ □ | □ □ □ | □ | Fourth interphalangeal joint | □ | □ □ □ | □ □ □ |
| □ □ □ | □ □ □ | □ | Fifth interphalangeal joint | □ | □ □ □ | □ □ □ |

**Note: ①1= Yes, 2= No, 3= Not done; ② NE = Not Evaluable;**
